**Fig. 2 Fig2:**
[figure not shown]
Comparison of current supply chain model (non-contraceptive commodities) and intervention supply chain model (contraceptives). SDP: Service Delivery Point; 3PL: Third-Party Logistician

*The intervention supply chain model* (also shown in Fig. 2) is being implemented by non-profit organisation IntraHealth International with funding from the Gates Foundation and MSD for Mothers, with the aim of improving the availability of FP commodities at public SDPs throughout Senegal. Private companies are contracted as third-party logisticians (3PL) to deliver FP commodities from regional storerooms directly to SDPs, bypassing the district level (thereby level-jumping). 3PLs make monthly deliveries to SDPs, during which they perform a stock inventory, top up contraceptive stocks to a level calculated based on consumption (around 3 months of stock), and collect data to forecast future delivery quantities. 3PLs are contracted by the implementer under fixed-fee performance-based contracts, with incremental penalties based on stock-out levels, re-supply delay and data availability [9]. Quarterly audits of 10 % of SDPs are conducted by the implementer to verify 3PL performance.

Eight products were initially included for distribution in the intervention (the combined pill, progesterone-only pill, injectable, implant, intra-uterine device (IUD), cycle beads, and male and female condoms), to which emergency contraception and a new sub-cutaneous injectable (Sayana Press) were added later. The initial stock of contraceptives is provided to SDPs at no cost, thus SDPs pay in arrears only for products sold, rather than paying upfront as in the current supply chain model [9]. A margin from the sale of FP commodities to women is retained at the SDP, district and regional levels, and 50 % of the margin is retained at the national level.

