The second study will be a 4-year monthly time series of contraceptive stock availability (objective 1.1) and FP consumption (objective 1.2), constructed from data from a sample of SDPs. Five of the 13 regions where the intervention was implemented by 3PLs (i.e. excluding Saint Louis) will be randomly selected, and 10 districts randomly selected in each region with probability proportional to the number of SDPs in the district. In each selected district, the health centre will be included, as well as three randomly selected health posts, for a total sample of 200 SDPs across urban and rural locations. There is limited guidance on sample size calculations for time series analysis, which usually focuses on the number of time points rather than of sampling units [49]. At least 48 monthly observations on stock inventory and FP consultations will be collected from each SDP, as well as from the selected district and regional storerooms, and the national-level storeroom, ensuring at least 24 monthly time points pre- and post-intervention.

Information on contraceptive stock availability will be extracted from stock cards, daily patient registers and stock journals, as well as for several ‘tracer’ stocks (anti-malarials, oral rehydration salts, amoxicillin, and iron tablets) not expected to change as a result of the intervention. Monthly number of FP consultations in which patients receive a contraceptive at the SDP will be extracted from patient registers. A time series analysis will be conducted by constructing a generalised linear segmented regression model of the probability of stock-out for any method on a given month, and for the most popular short-, medium- and long-acting methods. We will examine whether there is a change in the slope or level of the number of methods available and monthly FP consumption at SDPs between the pre- and post-intervention periods. This analysis will be repeated for the tracer stocks to compare their change in stock availability with FP methods as a proxy measure of the ‘normal’ distribution channels through which these commodities are still distributed.

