### Economic evaluation (Objective 4)

The purpose of the economic evaluation is to estimate the cost of the intervention (including costs related to capital goods, training, 3PL distribution, and audit teams), and its cost-effectiveness in relation to the current supply model. A micro-costing approach will be used to estimate the cost of the intervention and current supply chain models at national, regional, district, and SDP levels. Costs for 3PLs will be measured as the price paid for by the implementer. Costs will be estimated for the entire supply chain, retrospectively to capture costs pre­intervention, start­up costs (including initial training) and costs post­intervention.

A survey of SDPs and district, regional, and national storerooms will be conducted to measure costs. Among the SDPs included in objective 1, up to 80 SDPs will be randomly sampled to include a range of SDP sizes and rural/urban locations; the district and regional storerooms in which these SDPs are located will also be surveyed. A questionnaire will be administered to SDP and storeroom managers in order to record staff involved in supply chain management, time and resources spent collecting stock from higher-level storerooms, and intervention-related activities such as training. Financial and economic costs of the intervention and the current supply chain system will be collected through document reviews and account classification. The development of the survey tools will be informed by the in-depth interviews conducted during the process evaluation (objective 2) in order to ensure all costs are captured.

In addition, a time and motion study will be conducted to directly measure and cost time required to manage, operate and deliver the commodities to SDPs. Data on human resource utilisation and flow of services relating to the FP supply chain will be collected through interviews with SDP managers and 3PLs, and time spent on supply chain activities will be estimated using structured observations of SDP staff involved in supply chain activities and 3PLs and self-reported timesheets.

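### The two-period segmented regression lets the last months before rollout steer the projected pre-trend, although facilities that expected free initial stock would have had a cash-flow reason to let paid orders lapse

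*Protocol article*

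**What the plan says.** All references are to the protocol article.

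- **Methods, Outcome and impact evaluation (Objective 1), second study.** A generalised linear segmented regression models the monthly probability of stock-out. It is used to see "whether there is a change in the slope or level of the number of methods available and monthly FP consumption at SDPs", comparing the period before with the period after the intervention. On length: "At least 48 monthly observations on stock inventory and FP consultations will be collected from each SDP", "ensuring at least 24 monthly time points pre- and post-intervention". The same model is fitted to tracer commodities that stay on the usual distribution channel.
- **Design of the intervention, current model.** Facilities (SDPs) start orders themselves by sending stock requests to the district.
- **Design of the intervention, intervention model (text under Fig. 2).** "The initial stock of contraceptives is provided to SDPs at no cost", and "thus SDPs pay in arrears only for products sold, rather than paying upfront as in the current supply chain model".
- **Design of the intervention, rollout.** Eleven regions were added in stages between 2013 and March 2015.
- **Economic evaluation (Objective 4).** Start-up costs include initial training, and the costing questionnaire asks about "intervention-related activities such as training". Effectiveness for the cost-effectiveness ratios is taken from Objective 1.

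**The concern.** A segmented regression estimates the effect as the post-period fit minus the pre-period line carried forward. The pre-months nearest the switch have high leverage on that line. If they are unusual, the distortion is projected over the whole post-period.

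The payment terms give a reason why they might be unusual. Under the pull model an order costs the facility cash at once, and after rollout the first stock costs nothing. A facility that knew both the date and the terms could ease its cash flow by ordering less and waiting. Stock-outs would then rise, and methods available and consumption would fall, just before the switch. The fitted pre-trend would tilt against the intervention's absence, and both the level and slope changes would look better than they are. The same inflated effect would pass into cost per stock-out averted under Objective 4.

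No stated safeguard removes this from the fitted line. The fractional intervention variable belongs to the stepped-wedge study and handles delay after rollout. The limitations in the Discussion cover strike-related data gaps, concurrent family planning activities and changes to the intervention, but not behaviour in anticipation of it.

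**Working it through.** **Plan's own figures.** "Five of the 13 regions where the intervention was implemented by 3PLs" and "10 districts randomly selected in each region", with one health centre and three health posts per district: 5 × 10 × (1 + 3) = 200 SDPs. Series length: 24 + 24 = 48 months. Both reproduce. No effect size or power is stated for this study.

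**Model checked.** Linear segmented regression on months 1 to 48, break at 24.5, with intercept, trend, level change and slope change. The true series is flat, and stock-outs are raised by d points in the last k of the 24 pre-months. Both k and d are assumptions; the article gives neither. d is the rise averaged over all sampled SDPs, so if only some lapse, d shrinks in proportion.

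**Bias.** The pre-months have mean 12.5 and sum of squares 24 × (24² − 1)/12 = 1150.

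- Spurious pre-slope: b = k × (mean month of the dip − 12.5)/1150 × d
- Shift of the pre-period mean: (k/24) × d
- Bias in the level change (at 24.5): (k/24)d + 12b
- Bias in the mean effect over 24 post-months (centre 36.5): (k/24)d + 24b

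For k = 3 the dip is centred on month 23: b = 3 × 10.5/1150 = 0.0274d per month. Level: 0.125d + 12 × 0.0274d = 0.45d. Mean effect: 0.125d + 24 × 0.0274d = 0.78d.

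| Dip length k | Slope bias per month | Mean-effect bias | Bias of a plain pre/post mean |
|---|---|---|---|
| 1 | 0.010d | 0.28d | 0.04d |
| 2 | 0.019d | 0.54d | 0.08d |
| 3 | 0.027d | 0.78d | 0.125d |
| 6 | 0.047d | 1.38d | 0.25d |

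For k = 3, extrapolation makes the bias about six times that of a plain mean comparison (0.78/0.125). With the k months kept out of the pre-trend, the bias is 0 for each k.

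**Logit version.** The plan models a probability, so the check was repeated with a binomial logit model. The scale was borrowed from the Dakar figures in the article: 23 % baseline, 43 % in the dip months, 2 % after rollout. These are percentages of days stocked out, and using 43 % for a dip is an assumption. With k = 3 and a true fall of 21.0 points, the model returns 38.6 points. With no true effect it returns a 17.6-point reduction.

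**Precision cost of a separate 3-month window** (independent errors, in units of the residual SD).

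- Level change, 24 pre-months: √[2 × (1/24 + 12²/1150)] = 0.578.
- Level change, 21 pre-months (mean 11, sum of squares 770): √[(1/21 + 13.5²/770) + (1/24 + 12²/1150)] = 0.672, which is 16 % more.
- Mean effect, 24 pre-months: √[(1/24 + 24²/1150) + 1/24] = 0.764.
- Mean effect, 21 pre-months: √[(1/21 + 25.5²/770) + 1/24] = 0.966, which is 26 % more.
- With 3 earlier months added (24 pre-months ending at month 21): 0.636 and 0.847, about 10 % and 11 % above the first values.

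**The case against.** The strongest reply is that nothing in the article supplies d. The mechanism needs SDPs to know their date, to know the payment terms, to prefer running down stock, and to do so widely enough to move a 200-SDP average. None of this is documented. The training reference comes from a costing questionnaire and does not place training before rollout. SDPs still pay for what they sell, so the gain is mostly one of timing, and a lapsed order also forgoes sales. For the any-method outcome there may be little room for a rise, since implants alone were out on 83 % of days in two Dakar districts before the intervention. Windows around the break are often set in an analysis plan, and this is a condensed article. All of this stands. It is why the point is conditional and asks only for a sensitivity analysis.

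A reader might also infer that the tracers cannot reveal such a dip because they receive no free stock. The design does not support that. A parallel tracer series that stays level while contraceptives fall is what would expose a contraceptive-only dip. The tracers would not, however, take the dip out of the fitted contraceptive trend.

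Other parts of the evaluation help too: the stepped-wedge study uses fixed time effects and does not extrapolate a pre-trend, storeroom records are collected, and interviews look for unanticipated issues. These give context, but they do not correct the time-series estimate.

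What does not fall away is that the article states a two-period level-and-slope comparison alongside payment terms that change at the same break.

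**Conclusion.** The point holds conditionally. As described, the model lets the last pre-rollout months shape the extrapolated trend, and the payment terms give a plausible reason for those months to be atypical. If stock-outs rose by d in the last 1 to 6 of 24 pre-months, the mean 24-month effect would be overstated by 0.28d to 1.38d; for 3 months the level change would be overstated by 0.45d. The direction favours the intervention.

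This rests on the minimum series length, a break at each region's start, a linear model, and assumed values of k and d. The 24-month mean is a summary used here; the article names level and slope.

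A reader might go further and conclude that orders did lapse, that the result will be inflated by some definite number of points, or that the article declares every pre-rollout month to be ordinary pull distribution. The document supports none of these. It reports no dip and no advance notice, and its reference to normal channels concerns the tracers.

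**What to change.** Keep the stated model as primary. Prespecify one sensitivity analysis in which a short window before each region's start has its own segment and does not inform the pre-trend. Three months is a workable default, varied from 1 to 6, or the window can begin at the training or announcement date if that is known. Report both models.

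Plot contraceptive and tracer stock receipts by month relative to rollout, from the SDP and storeroom records already being extracted. The planned interviews with health workers and stock managers can ask when facilities learned of the date and the terms.

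If the two models differ materially, temper the conclusion. Do not let the data choose the headline model, since a late pre-rollout decline could also be genuine deterioration.

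The cost is analysis wording and no new sites. In the sensitivity model the standard error rises by about 16 % for the level change and 26 % for the mean effect with 21 pre-months. Three earlier months bring this down to about 10 % and 11 %, and the stated minimum of 48 months allows them. In some regions they may fall in the 2010–2012 strike period that the Discussion flags, so their quality should be checked in the planned data quality pilot before they are relied on.

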There are several limitations to our approach. First, our ability to investigate contraceptive stock supply over time relies on the availability of good quality stock data in SDPs. Between 2010 and 2012, health staff in some regions of Senegal took strike action which manifested as a refusal to send health data to the district level, which may affect data availability for the time series study in regions where the 24-month pre-intervention period includes 2011–2012. Health facility and staff adherence to the strike was variable, and it is unclear whether stock data were particularly affected since a different cadre of staff (community-funded “dépositaires”, or stockists) is tasked with completing stock cards, rather than the centrally-funded nursing staff who were on strike. In addition, it is not clear whether, given the duration of the strike, data continued to be collected but were not sent upward or whether nursing staff and stockists stopped recording data in SDPs. The availability of good data in SDPs will be explored in the data quality pilot study prior to collecting data for the time series.

Second, estimating the contribution of the intervention to any observed increase in contraceptive use may be challenging given that other FP-related activities such as demand-generation activities, public endorsements of FP by community leaders, and outreach activities are implemented throughout the country. The evaluation methodology is designed to take this limitation into account as effectively as possible. The staggered rollout of the intervention across regions will enable us to estimate more precisely the effect attributable to the intervention. As part of the assessment of contextual factors (objective 3), we will further estimate the implementation intensity of FP-related activities in order to disentangle the potential effect of the intervention and of other FP-related activities on the MCPR.

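### As described, the monthly FP consumption series is an uncontrolled pre/post segmented regression, so an abrupt national change in demand would be read as an intervention effect

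*Protocol article*

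**What the plan says.** The second study in the Protocol article's section on the outcome and impact evaluation (Objective 1) builds monthly series from a sample of SDPs, "for a total sample of 200 SDPs across urban and rural locations", and "ensuring at least 24 monthly time points pre- and post-intervention".

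- **Consumption data:** "Monthly number of FP consultations in which patients receive a contraceptive at the SDP will be extracted from patient registers". No other consultation series is named.
- **Model:** "A time series analysis will be conducted by constructing a generalised linear segmented regression model". The question asked is whether slope or level changes in the number of methods available and in "monthly FP consumption at SDPs between the pre- and post-intervention periods".
- **Comparison series:** "This analysis will be repeated for the tracer stocks to compare their change in stock availability with FP methods".

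The Discussion lists as a limitation that "demand-generation activities, public endorsements of FP by community leaders, and outreach activities are implemented throughout the country". Its answer is: "The staggered rollout of the intervention across regions will enable us to estimate more precisely the effect attributable to the intervention". The stepped-wedge model of the first study, fitted to the annual facility and household surveys, puts that answer into practice.

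**The concern.** The tracer products (anti-malarials, oral rehydration salts, amoxicillin, iron) can show whether ordinary distribution improved over the same period. They carry no information on how many women came for contraception. The stock series therefore has a control and the consumption series has none.

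A segmented regression attributes to the intervention any departure from the extrapolated pre-rollout line. If a campaign or public endorsement lifted demand across the country at one date, each region would show a departure whose size and sign depend on where that date falls in its own 48-month window.

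The stakes reach beyond the series itself. The Economic evaluation section takes incremental effectiveness from Objective 1, and Table 3 sources couple-years of protection from the SDP survey and document review. A biased consumption effect can thus enter the cost-effectiveness ratios.

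**Working it through.** **The plan's own figures.** 5 regions × 10 districts × (1 health centre + 3 health posts) = 200 SDPs, and 24 + 24 = 48 months. Both reproduce. No effect size, variance or power is given for this series, so the check concerns bias only.

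**Assumptions.** The article gives start waves by year and a last start in March 2015, not exact months. With month 0 = January 2011, I took five regions starting at months 24, 40, 42, 50 and 50 (early 2013, two in 2014, two in March 2015), each with 24 + 24 months. The true intervention effect is zero. Log consumption steps up by 0.15 everywhere at month 30 (mid-2013). There is no noise, so what the fit returns is bias.

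**Segmented model**, for a region starting at month s:

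y(t) = b0 + b1(t − s) + b2·1[t ≥ s] + b3·(t − s)·1[t ≥ s]; effect at 12 months = b2 + 12·b3.

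| Start month | False 12-month effect (log scale) |
|---|---|
| 24 | +0.116 |
| 40 | -0.136 |
| 42 | -0.155 |
| 50 | -0.103 |
| 50 | -0.103 |

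Pooled: (0.116 − 0.136 − 0.155 − 0.103 − 0.103) / 5 = −0.381 / 5 = -0.076.

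The sign flips because the step falls after rollout in the first region and before it in the others. There it steepens the fitted pre-slope, and the flat post-period then looks like a shortfall. Moving the step across months 18 to 48 shifts the month-24 region between -0.06 and +0.15, and the month-50 regions between -0.16 and +0.07. A step in the start month itself is reported in full as a level change. A purely linear national trend gives zero bias, since b1 absorbs it.

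**Calendar-month model** (region effects, common calendar-month effects, rollout indicator), same data: bias 0.000, with or without a post-rollout slope.

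**Limits of that model.**

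- *Concurrent comparators.* Of 5 × 24 = 120 post-rollout region-months, those with an unswitched region under observation number 24 + 10 + 8 + 0 + 0 = 42, or 35 %.
- *Estimability.* With minimum windows, two regions whose starts differ by 6, 12, 18 or at least 24 months share 18, 12, 6 or 0 untreated months. If the only starts are months 24 and 50, or all starts coincide, the effect cannot be estimated.
- *Growing effect.* If the true effect rises linearly to 0.20 over 12 months (24-month average 0.154), a level-only calendar-month model returns 0.060.
- *Effects that differ by region.* With constant regional effects of 0.3, 0.2, 0.2, 0.1 and 0.1 (mean 0.18), a common level-plus-slope model gives 0.258 at 12 months.

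**Will the sample have staggered starts?** Without Saint-Louis the waves hold 3, 5 and 5 regions (note to Fig. 1). Of the C(13,5) = 1,287 draws, 2 lie in a single wave, 360 span two and 925 span three. Draws confined to the early-2013 and 2015 waves, where starts may be 24 or more months apart, number C(8,5) − 1 = 55 (4.3 %).

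**The case against.** The strongest reply is that a condensed article gives the time-series model one sentence, so missing calendar terms may simply be left to an analysis plan. That stands as far as model terms go: how the regions are pooled is not stated, and silence does not show that the start dates play no part. It does not remove the point, because the article does choose a comparison series and confines it to stock availability, while it describes the consumption question purely as pre against post.

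Two stronger readings are tempting and not supported.

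- A reader might infer that the evaluation ignores the staggered rollout and so contradicts its Discussion. It does not. The first study models the stagger for stock availability and, from the household surveys, for contraceptive use. The Discussion's sentence on the rollout concerns contraceptive use and its paragraph ends on the population prevalence rate. It also treats the 24-month pre-period as specific to each region. Objective 1.2 as a whole has a between-region contrast; the monthly consumption series is what lacks one.
- A reader might infer that every national change in demand becomes bias. Linear trends are absorbed, and a step outside a region's window has no effect.

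It is also fair to say that single-region figures overstate the pooled bias (-0.076 here), and that a naive calendar-month model can itself be badly wrong when effects grow or differ by region. The article anticipates both: its first study allows for delayed and regionally varying effects.

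**Conclusion.** The point holds in a limited form. As described, the FP consumption series has no comparator for demand, and abrupt or non-linear national changes within a region's window would be read as intervention effect. The article itself makes such changes plausible.

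Under the assumed 0.15 step, its mid-2013 date and the assumed start months, the false 12-month effect is +0.12 to -0.16 by region and about -0.08 pooled. These figures illustrate size only. That size and sign vary with rollout date follows from the model and not from the particular step chosen.

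The staggered starts offer a usable partial control, but not a free one: it is concurrent for only part of the post-rollout period and rests on five regions whose timing was not randomised.

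**What to change.** Keep the segmented model and add a second FP-consumption analysis:

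1. Include region or SDP effects and calendar-month effects common to the sampled regions.
2. Extract the sampled regions over a common calendar window where registers allow, rather than only 24 + 24 months around each start.
3. Let the effect vary with time since rollout (level plus slope, or event-time terms) and by region.
4. Base the controlled estimate on months when at least one sampled region has not yet switched.
5. Label the uncontrolled segmented estimate as descriptive, including wherever it feeds couple-years of protection and the cost-effectiveness ratios.

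The cost is mostly analysis wording, plus some extra register months: up to 24 for a March 2015 region if it is to match the full pre-period of an early-2013 region. Intervals will be wider. There is no concurrent control after the last sampled region starts. The controlled effect may not be estimable if the sampled starts coincide, or if they fall only into groups about 24 or more months apart and minimum windows are kept. Common calendar-month effects give no protection against co-interventions that differ by region, so the planned stratification by intensity of other FP activities is still needed.
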